## Abstract

**Background/Objectives:** Chronic pain in older adults is a highly disabling epidemic, often overtreated with passive pharmacological approaches. Although clinical guidelines recommend active strategies combining multicomponent exercise and Pain Neuroscience Education (PNE), robust geriatric evidence remains scarce. Therefore, the central objective of this randomized controlled trial (RCT) is to evaluate the efficacy of combined PNE and exercise versus exercise alone. Crucially, this RCT addresses a major literature gap by investigating the long-term dose–response effect of PNE (an 8-week intensive vs. a 32-week maintenance program) to determine the optimal strategy for sustaining behavioral change and pain relief. **Methods:** A prospective, single-blind RCT (1:1:1 allocation) will recruit 90 older adults (≥65 years) with primary chronic musculoskeletal pain. The 32-week intervention comprises three arms: a control group (multicomponent exercise), Intervention Group 1 (exercise + 8 weeks of PNE), and Intervention Group 2 (exercise + 32 weeks of PNE). The primary outcome is pain intensity (assessed via the Numeric Rating Scale [NRS]). Secondary outcomes include kinesiophobia, pain catastrophizing, chronic pain grade and related disability, quality of life, physical performance, body composition and analgesic consumption. Data collected at baseline, 8, and 32 weeks will be analyzed using mixed-effects models for repeated measures. **Results:** As this is a study protocol, there are no results to report yet. Upon completion of the trial, data will be analyzed using mixed-effects models for repeated measures to evaluate intra- and intergroup changes over time, and the findings will be disseminated in future publications. **Conclusions:** By evaluating the long-term dose–response effect, this study will determine the optimal PNE dosage required for sustained pain relief and behavioral change in older adults. If our hypotheses are confirmed, the findings will generate high-quality evidence to support the integration of combined active interventions into community settings, promoting active aging and reducing the burden of chronic pain. **Trial Registration:** ClinicalTrials.gov Identifier: NCT07287501.

## 1. Introduction

Population aging constitutes a major public health challenge, with chronic pain standing out as a highly prevalent and disabling condition. Approximately 36.6% of older adults suffer from persistent pain, which negatively impacts their mobility, autonomy, and mood, increasing the risk of frailty, falls, and cognitive decline [1,2,3,4,5,6,7]. Pathophysiologically, chronic pain in this population is a complex phenomenon driven by age-related central sensitization and maladaptive neuroplasticity, where pain loses its protective function [8,9]. Furthermore, psychosocial factors such as kinesiophobia (fear of movement) and pain catastrophizing play a critical role in its chronification, perpetuating a vicious cycle of inactivity, physical deconditioning, and functional disability [10,11,12,13].

Despite its multidimensional nature, the therapeutic approach often remains predominantly biomedical and pharmacological, posing significant risks of polypharmacy and adverse effects in older adults [14,15]. Consequently, current clinical guidelines strongly advocate a paradigm shift toward active, non-pharmacological interventions, highlighting therapeutic exercise and PNE to facilitate active coping [16,17,18,19,20,21,22,23,24].

PNE aims to reconceptualize the pain experience by explaining the underlying neurophysiological mechanisms (such as central sensitization and neuroplasticity), thereby reducing the perception of threat and facilitating an active coping approach [25,26]. Conceptually, PNE is deeply rooted in the Fear-Avoidance Model and cognitive–behavioral frameworks [27]. By explaining the neurobiology of pain, PNE successfully reduces pain catastrophizing and kinesiophobia [28,29]. Recent mediation analyses demonstrate that this reduction in fear of movement is the primary mechanism leading to long-term functional recovery [30]. By disrupting avoidance behaviors, PNE significantly increases patients’ pain self-efficacy (their confidence to move despite the pain) [31]. This enhanced self-efficacy acts as the crucial cognitive–behavioral catalyst that fosters greater long-term adherence to active treatments, such as multicomponent exercise programs [32].

Current evidence strongly supports this combined approach across diverse clinical populations. Recent meta-analyses and trials demonstrate that combining PNE with physical exercise yields significantly greater short- and long-term improvements in pain intensity, disability, and kinesiophobia compared to exercise alone in patients with chronic spinal pain, chronic neck pain, and fibromyalgia [28,33,34,35]. By effectively reducing the perceived threat value of pain and promoting active coping, PNE has established itself as a cornerstone in modern pain management. In the older adult population, emerging trials confirm that adapted PNE programs can effectively improve physical function, step count, and fear-avoidance beliefs [36,37]. However, despite these promising findings, robust empirical evidence adapted to the specific cognitive and physical needs of the geriatric population remains scarce. Previous studies in older adults often present substantial methodological limitations, high heterogeneity, and a lack of long-term follow-ups [38,39,40,41]. Furthermore, beyond these methodological constraints, a major scientific gap remains regarding the optimal dosage of educational interventions required to modify deeply rooted beliefs and sustain behavioral changes over time in geriatrics. A recent dose–response meta-analysis identified that at least 150 to 200 min of PNE are needed to achieve clinically important changes in pain and disability [42], yet long-term comparative studies directly evaluating maintenance protocols in older adults are lacking.

Therefore, this study protocol describes a randomized controlled trial aiming to evaluate the efficacy of a combined program of PNE and multicomponent exercise compared to exercise alone in older adults with chronic pain. Specifically, we will investigate the dose–response effect of PNE by comparing a short-term intensive phase (8 weeks; 240 min) versus a long-term maintenance program (32 weeks; 360 min). The primary objective of this trial is to determine the effectiveness of these interventions in reducing pain intensity, ultimately helping to establish the optimal strategy for sustaining long-term pain relief and promoting active aging.

## 2. Materials and Methods

### 2.1. Study Design

This study has been designed as a prospective, longitudinal, randomized controlled trial with three parallel groups and a 1:1:1 allocation. The protocol follows the guidelines of the CONSORT (Consolidated Standards of Reporting Trials) statement for non-pharmacological clinical trials [43]. The study will have a total duration of 12 months, with a 32-week intervention period. The flow of participants through each stage of the trial is depicted in Figure 1.

### 2.2. Participants and Eligibility Criteria

The study population will consist of community-dwelling older adults aged 65 years or older (Salamanca, Spain), recruited through the “Programa de Revitalización Geriátrica (PReGe)”. Inclusion criteria are as follows: (1) age ≥65 years; (2) history of primary chronic musculoskeletal pain lasting more than 3 months; (3) pain intensity ≥3 out of 10 on the Numeric Rating Scale (NRS) [44,45]. Exclusion criteria are as follows: (1) presence of secondary chronic pain conditions (e.g., oncological pain, specific rheumatic diseases such as ankylosing spondylitis or rheumatoid arthritis, fibromyalgia, neuralgias, and nerve injuries or neuropathies such as carpal tunnel syndrome); (2) severe psychiatric pathologies; (3) uncontrolled systemic, inflammatory, or cardiac diseases; or (4) other medical conditions that contraindicate physical exercise.

### 2.3. Randomization and Blinding

Following the baseline assessment, eligible participants will be randomly assigned to one of the three study groups using a computer-generated sequence (R software version 4.2.1; R Foundation for Statistical Computing, Vienna, Austria), utilizing a block randomization design to ensure balance between the groups. Allocation will be performed by an independent researcher uninvolved in the recruitment process. Due to the nature of the intervention (exercise and education), it is not possible to blind the participants or the therapists. However, a single-blind design will be employed: the evaluators in charge of recording the outcome variables will be unaware of the group allocation, and the statistical analysis will be performed by an independent researcher using coded data, ensuring they also remain completely blinded to the group distribution and allocation.

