### 2.6. Sample Size and Statistical Analysis

The sample size was calculated based on the primary outcome (pain intensity via NRS). The estimation was performed using the GRANMO Version 8.0 tool. We calculated the effect size based on a Minimal Clinically Important Difference (MCID) of 1.5 points and a common standard deviation of 1.8. Assuming a two-sided contrast and an Analysis of Variance (ANOVA) for three independent groups, with an alpha level of 0.05, a statistical power of 80%, and an anticipated dropout rate of 10%, a minimum of 30 participants per group is required, resulting in a total sample of 90 subjects.

Intention-to-treat analysis will be performed. The primary endpoint for determining the long-term efficacy of the interventions is defined as the change in the primary outcome (NRS) at 32 weeks. Mixed-effects models for repeated measures will be used to evaluate intra- and intergroup changes over time (T0, T1, T2), considering the Group × Time interaction. To adjust for initial variance, baseline values of each respective outcome will be included as covariates in all models. Within this modeling framework, missing data will be inherently handled using restricted maximum likelihood (REML) estimation under the missing-at-random assumption. Additionally, to control for the inflation of Type I error associated with the analysis of multiple secondary outcomes, the Benjamini–Hochberg False Discovery Rate procedure will be applied. Furthermore, a secondary analysis stratified by sex will be conducted to evaluate potential differences in the intervention’s efficacy between men and women. Additionally, baseline TMT scores will be utilized as a covariate in an a priori secondary analysis to determine if baseline levels of executive function and cognitive flexibility modulate the treatment outcomes. The significance level will be set at *p* < 0.05.

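### No stratification by sex is stated for the randomisation, although an efficacy analysis stratified by sex is planned: a minor mismatch that is cheap to mend

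*Protocol article*

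**What the plan says.** Section 2.1 sets out "three parallel groups and a 1:1:1 allocation", and section 2.6 says that "a minimum of 30 participants per group is required, resulting in a total sample of 90 subjects".

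Section 2.3 gives the allocation method: a computer-generated sequence in R, produced after the baseline assessment, "utilizing a block randomization design to ensure balance between the groups". It states neither a stratification factor nor a block size.

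Section 2.6 then says that "a secondary analysis stratified by sex will be conducted to evaluate potential differences" in efficacy between men and women. On adjustment, it says that "baseline values of each respective outcome will be included as covariates in all models". The Trail Making Test score is added as a covariate in one further secondary analysis. Sex is not named as a covariate anywhere.

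The eligibility criteria in section 2.2 set no condition on sex, and no expected proportion of men or women is given.

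**The concern.** A 1:1:1 permuted block fixes how many people enter each arm. It does nothing to fix how many of them are men. The plan compares the arms within each sex, sex is known before allocation, and the list is generated by computer, so balancing sex across arms would cost almost nothing. As described, the number of men per arm is left to chance.

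What is at stake is the precision of a secondary analysis. If one sex is a minority, its cells are small to begin with, and an unlucky list can leave one arm with half as many of that sex as another. The trial is run once, on one list, so the spread of possible lists matters as well as the average. The list cannot be changed once randomisation has started, so the point is best settled before then.

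**Working it through.** **Inputs from the protocol article.** Three arms, 1:1:1, 30 per arm (sections 2.1 and 2.6). The planning values are a "Minimal Clinically Important Difference (MCID) of 1.5 points and a common standard deviation of 1.8" (section 2.6).

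**Assumptions.** Block size 6 and a share of men from 10% to 50%; the article states neither.

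**The plan's own sample size.** Section 2.6 starts from "Assuming a two-sided contrast and an Analysis of Variance (ANOVA) for three independent groups", with alpha 0.05, power 80% and 10% dropout, but not the pattern of the three means.
- Means 0, 0.75, 1.5: variance of the means = (0.75² + 0 + 0.75²)/3 = 0.375, so f = √0.375/1.8 = 0.340. This needs 29 per arm; 29/0.9 = 32.2, so 33.
- Means 0, 0, 1.5: variance of the means = 0.5, so f = √0.5/1.8 = 0.393. This needs 22 per arm; 22/0.9 = 24.4, so 25.

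The stated 30 lies between 25 and 33. It cannot be reproduced exactly without the pattern of means, and it is not faulted here.

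**Step 1: men per arm.** Simulated trials of 90 participants, with sex drawn independently at the assumed share. Unstratified blocks of 6 are compared with sex-stratified blocks of 6.

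| Assumed share of men | Largest arm has at least twice the men of the smallest: no strata | Same: sex strata | Mean gap, largest minus smallest: no strata | Same: sex strata |
|---|---|---|---|---|
| 15% | about 60% | about 6% | 3.3 men | 0.9 |
| 25% | about 35% | 0% | 4.0 men | 0.9 |
| 35% | about 18% | 0% | 4.4 men | 0.9 |
| 50% | about 4 to 5% | 0% | – | – |

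At 25% men, some arm has 4 or fewer men in about 26% of trials without strata and 4% with. At 50% men, a gap of 4 or more men is still common (about 63%), but each arm then has about 15 men, so the ratio is rarely extreme. With strata and blocks of 6, the gap never exceeds 2.

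**Step 2: what this costs in power.** For a pairwise comparison among men with m per arm, before dropout: SE = 1.8 × √(2/m), and power = Φ(1.5/SE − 1.96). For m = 6: SE = 1.8 × √(2/6) = 1.04, 1.5/1.04 = 1.44, and power = Φ(−0.52) = 30%.

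| Share of men | Men per arm if even | Power, exactly even | Average power, no strata |
|---|---|---|---|
| 20% | 6 | 30.3% | 28.5% |
| 30% | 9 | 42.4% | 40.9% |
| 50% | 15 | 62.6% | 61.8% |

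The average gain is 1.8, 1.5 and 0.8 points. The normal approximation flatters cells this small, so true power is lower in both columns.

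**Step 3: the bad draws.** At 25% men, the 95th percentile of the SE for a pairwise difference among men falls from about 1.24 without strata to about 1.09 with them.

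**Step 4: the interaction.** Take a 1.5-point difference between the sexes in a pairwise treatment effect, with men spread evenly: SE = 1.8 × √(2/m + 2/(30 − m)). At 20% men this is 1.8 × √(2/6 + 2/24) = 1.16, with power of about 25%. At 50% men it is 1.8 × √(2/15 + 2/15) = 0.93, with power of about 36%. Even with perfect balance the sex analysis is weak.

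**The case against.** The strongest case against is that this is a design preference and not an error. Several parts of it stand.

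- **Silence in a condensed article.** The article may omit a stratification factor that the full protocol contains. One can say only that none is stated, not that stratification was ruled out.
- **The meaning of balance.** Beside a 1:1:1 ratio, the sentence on blocks is fairly read as balance in group size, which blocks do deliver. A reader might infer that the article claims covariate balance; the text does not require that reading.
- **The share of men.** A reader might infer that men will be few. Nothing in the documents says so, and near an even split a twofold imbalance is rare.
- **Validity.** A reader might infer that a sex-stratified analysis needs sex-stratified allocation. It does not: comparisons within each sex remain randomised.
- **Precision.** Even 4 men against 10 gives SE = 1.8 × √(1/4 + 1/10) = 1.07, against 1.8 × √(2/7) = 0.96 for 7 and 7, which is about 11% wider.
- **The primary contrast.** A reader might infer that chance imbalance in sex harms the 32-week pain comparison. That needs sex to predict the outcome after adjustment for baseline pain, and the documents give no such figure. As an illustration, with 25% men and a 0.5-point sex difference, sex explains 0.25 × 0.75 × 0.5²/1.8² = 1.4% of the variance; with 1.0 point, about 6%.

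What remains is narrow. The plan itself chose sex as a dimension for judging efficacy, the allocation text does nothing stated to support that choice, and the remedy is close to free. An average gain of 1 to 2 points also understates the benefit, because stratification cuts off the worst lists.

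**Conclusion.** The point holds as a minor one. As described, allocation balances arm sizes only, while an efficacy analysis by sex is promised and sex is not listed as a covariate. If either sex is a clear minority, uneven cells are likely: a twofold imbalance in about 60% of trials at 15% and about 35% at 25%, against 6% or less with strata. These figures rest on an assumed block size of 6 and an assumed sex mix.

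The consequence is confined to the precision of one secondary analysis. The documents do not support reading this as a threat to the validity of the randomisation or to the primary result. Nor would stratification rescue the sex analysis: the number of participants per sex per arm is its main limit, and that number does not change.

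**What to change.** - **Before randomisation starts:** generate two permuted-block lists in R, one for men and one for women, each 1:1:1, and state sex as the stratification factor in section 2.3. If the full protocol already does this, say so in the article.
- **In the models:** add sex as a fixed effect beside the baseline value of the outcome.
- **For the sex analysis:** report it as an exploratory sex-by-group interaction with confidence intervals, and not as separate significance tests in men and in women.
- **If randomisation has already begun:** keep the existing list and make only the two analysis changes.

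The cost is a second list, one model term and a few sentences. The downside is that an incomplete last block in each stratum can make arm sizes differ by a participant or two. Two strata in 90 participants is not over-stratification.

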### 2.4. Interventions

Interventions will be carried out at university facilities and municipal community centers. All groups will maintain their usual pharmacological treatment and activities of daily living. All interventions will be delivered by physiotherapists who received specific and standardized training in pain neurophysiology and therapeutic education for chronic pain during the pre-clinical phase of the study to ensure treatment homogeneity.

The PNE protocol was meticulously designed based on current high-quality evidence. Specifically, the selection of the thematic contents is grounded in the latest international Delphi consensus on therapeutic pain education [46]. Furthermore, the two-phase pedagogical structure and the use of active constructivist methodologies during the maintenance phase are justified by the educational frameworks recently described by the PETAL collaboration [24] to maximize long-term behavioral change and self-efficacy. Phase 1 (weeks 1–8) focuses on reconceptualizing pain through interactive, age-adapted sessions explaining neurophysiological concepts (e.g., central sensitization, neuroplasticity, damage vs. pain). Phase 2 (weeks 9–32) employs active and constructivist methodologies (such as problem-based learning, clinical case resolution, and role-playing) to consolidate knowledge transfer to daily life activities. Thus, comparing a short-term PNE program with a long-term extended phase is not primarily intended to test a higher cumulative volume of information, but rather the efficacy of sustained engagement and periodic reinforcement in translating the initial reconceptualization of pain into long-term habits and pain self-management. The rationale for selecting these specific durations is twofold. First, the 8-week intensive phase (comprising 16 sessions of 15 min) provides a total educational dose of 240 min. This duration was specifically chosen to exceed the established efficacy threshold, as a recent dose–response meta-analysis concluded that at least 150 to 200 min of PNE are necessary to achieve clinically meaningful improvements in pain and disability [42]. Second, the 32-week duration was selected because it mirrors the standard 8-month academic cycle of municipal health and exercise programs for older adults in the community (such as the PReGe). This allows for a pragmatic evaluation of whether sustaining the educational reinforcement throughout an entire real-world community program cycle yields superior long-term adherence and behavioral changes. The specific characteristics of each arm are detailed in Table 1. The structure, content, and objectives of the multicomponent exercise program are detailed in Table 2, while the PNE session contents and their specific pedagogical objectives are summarized in Table 3. 

Control Group (CG-Multicomponent Training): They will undergo a multicomponent physical exercise program supervised by physiotherapists, based on the recommendations of the LIFE and SPRINTT studies [47,48]. Sessions will include a warm-up, aerobic exercise, muscle strength, balance/coordination and cool-down. Intensity will be individually adjusted using the Borg Rating of Perceived Exertion Scale (target range 5–7) [49]. Because this group receives a structured physical intervention, it functions as an active comparator rather than a traditional passive control. This baseline ensures that any expected between-group differences will specifically reflect the added value of the PNE interventions. The detailed structure, content, and objectives of the exercise sessions are presented in Table 2.Intervention Group 1 (IG1-Exercise + PNE 8 weeks): In addition to the same exercise protocol as the CG, participants will receive the Phase 1 PNE program during the first 8 weeks. These 15 min educational sessions will be delivered immediately before the exercise, using visual materials and supporting leaflets to facilitate active coping.Intervention Group 2 (IG2-Exercise + PNE 32 weeks): Participants will receive the same exercise program and the initial 8-week Phase 1 PNE program (identical to IG1). Subsequently, they will continue with the Phase 2 educational maintenance program until week 32. This phase consists of biweekly 15 min sessions delivered before the exercise, focusing on group dynamics and useful tools for pain management, such as dietary guidelines and relaxation techniques.

To ensure intervention fidelity and pedagogical standardization across all groups, PNE sessions will be strictly guided by a predefined intervention manual, using standardized visual aids and structured educational leaflets. To actively assess participant comprehension, a dedicated question-and-answer period will conclude each session, and specific knowledge verification questionnaires will be administered during sessions 7 and 14. Furthermore, from session 17 onwards, the implementation of active constructivist methodologies will allow the facilitator to continuously monitor engagement, identify and correct any cognitive misconceptions in real-time, and guide participants toward the accurate practical application of the concepts in their daily lives.

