### 2.5. Outcomes and Data Collection

Evaluations will be conducted at three time points: Baseline (T0), Intermediate at 8 weeks (T1), and Final at 32 weeks (T2).

Primary Outcome: The primary outcome will be pain intensity measured by the NRS [32,33].Secondary Outcomes: Psychosocial variables will include Kinesiophobia (Tampa Scale for Kinesiophobia, TSK-11) [50,51], Pain Catastrophizing (Pain Catastrophizing Scale, PCS) [52], chronic pain grade and related disability (Chronic Pain Grade Scale) [53], and health-related quality of life (SF-12) [54,55]. Physical performance will be evaluated using the Short Physical Performance Battery (SPPB) [56], the Timed Up and Go (TUG) test [57], handgrip strength (JAMAR Plus+ dynamometer; Performance Health, Warrenville, IL, USA) [58], and the force–velocity profile of the lower extremities (ADR linear encoder; ADR Inercial, Toledo, Spain) [59]. Changes in body composition (Tanita BC-418 Bioelectrical Impedance; Tanita Corporation, Tokyo, Japan) [60,61] and daily analgesic consumption will also be recorded. Additionally, adherence to the intervention will be rigorously monitored by recording participant attendance at all multicomponent exercise and Pain Neuroscience Education sessions. Finally, the Trail Making Test (TMT) will be administered at baseline to evaluate executive function and cognitive flexibility [62,63]. The inclusion of this instrument is based on an a priori secondary hypothesis that baseline levels of these capacities modulate the responsiveness to PNE, given that this educational intervention requires high cognitive flexibility to successfully reconceptualize the pain experience [22,26].

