From a methodological perspective, the design ensures that all participants in the three study arms benefit from a structured physical training program of the same duration and intensity. This guarantees an equivalent level of exposure to exercise, which will allow a rigorous and isolated evaluation of the true efficacy of PNE and its long-term dose–response effect. The study presents limitations inherent to non-pharmacological clinical trials, primarily the impossibility of applying double blinding (neither the participants nor the physiotherapist delivering the education can be blinded). However, this bias will be mitigated through a single-blind design, in which the evaluators in charge of data collection and the researchers performing the statistical analysis will be completely unaware of the group allocation.

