## 6. Conclusions

This study protocol outlines a rigorous randomized controlled trial designed to address a critical gap in the management of geriatric chronic pain by evaluating the long-term dose–response effect of PNE combined with multicomponent exercise. By prioritizing active coping strategies over traditional passive treatments, this trial provides an innovative approach specifically tailored to the neurocognitive and physical needs of older adults. If our hypotheses are confirmed, the findings will generate high-quality evidence to determine the optimal educational dosage required for sustained pain relief. Ultimately, this will support the integration of combined active interventions into community settings, representing a safe and low-cost alternative centered on patient empowerment, promoting active aging, and reducing the burden of chronic pain in our communities.

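### The trial compares two whole education programmes at week 32; it cannot deliver the promised isolated dose–response effect or optimal PNE dosage

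*Protocol article*

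**What the plan says.** The dose claim stands in four places in the Protocol article.

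- Section 1 (Introduction) sets out to study the "dose–response effect of PNE by comparing a short-term intensive phase (8 weeks; 240 min) versus a long-term maintenance program (32 weeks; 360 min").
- The Abstract concludes: "By evaluating the long-term dose–response effect, this study will determine the optimal PNE dosage required for sustained pain relief".
- Section 5 (Discussion) promises a "rigorous and isolated evaluation of the true efficacy of PNE and its long-term dose–response effect", on the ground that exercise is equal in all arms.
- Section 6 (Conclusions) expects evidence to "determine the optimal educational dosage required for sustained pain relief".

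Section 2.4 describes the same comparison differently: it "is not primarily intended to test a higher cumulative volume of information, but rather the efficacy of sustained engagement and periodic reinforcement".

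The design facts are these. IG1 receives 16 sessions of 15 minutes in weeks 1–8. IG2 receives the same sessions and then Phase 2, which Section 2.4 says continues to week 32 and which moves to problem-based learning, case work and role-play. All arms exercise for 32 weeks (Table 1). Section 2.5 lists assessments at baseline, at week 8 and "Final at 32 weeks (T2"), with none later. Section 2.6 places the primary endpoint, change in NRS, at week 32.

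**The concern.** One randomised comparison, IG2 versus IG1, is described as answering two different questions. The first is how much education is best. The second is whether continued reinforcement helps. Only the second matches the arms. The first needs programmes that differ in amount and are otherwise alike, at enough levels to locate an optimum.

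The word sustained raises a related question. IG1 and IG2 stand at different distances from their last teaching when the primary endpoint is measured, and IG2 is not observed after its programme closes.

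At stake is the headline conclusion. Section 6 expects the results to support integration into community settings. Someone planning the length of such a programme would take a statement about optimal dosage literally, although the trial would not have tested dosage as such.

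**Working it through.** **1. Stated doses (Section 2.4, Table 1, Table 3).** Dose = sessions × 15 min.

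- IG1: 8 weeks × 2 per week = 16 sessions; 16 × 15 = 240 min. This reproduces the stated figure.
- IG2 by the session list: 24 × 15 = 360 min. This also reproduces. Phase 2 then has 24 − 16 = 8 sessions, or 8 × 15 = 120 min, which is 120/240 = 50% more than IG1.
- IG2 by the stated frequency: weeks 9–32 are 24 weeks; at one session per two weeks, 24/2 = 12 sessions. The total is 16 + 12 = 28 sessions, or 28 × 15 = 420 min. The excess over IG1 is 180/240 = 75%. This does not reproduce the stated 360 min.

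Eight sessions spread over 24 weeks would be one every 24/8 = 3 weeks. The frequency and the total therefore contradict each other.

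**2. Time from end of education to the week-32 assessment.**

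- IG1: 32 − 8 = 24 weeks.
- IG2, if Phase 2 runs to week 32: about 0 weeks.
- IG2, if the eight listed sessions are held every two weeks: they fill 8 × 2 = 16 weeks and end near week 8 + 16 = 24, a gap of about 8 weeks.

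**3. What differs between IG1 and IG2.**

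| Feature | IG1 | IG2 |
|---|---|---|
| Minutes | 240 | 360 by the total, 420 by the frequency |
| Duration of education | 8 weeks | 32 weeks |
| Teaching method | Phase 1 explanatory sessions | Phase 1, then problem-based learning, case work, role-play |
| Education contacts | 16 | 24 or 28 |
| Gap to final assessment | 24 weeks | about 0 (or about 8) weeks |

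All five features change together, and there is one contrast. No arm holds any of them fixed while another moves, so their contributions cannot be separated. The aliasing lies in the arms themselves, so no later choice of model removes it.

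**4. Can an optimum be located?** The non-zero levels are 240 and 360 (or 420) min. Sections 1, 2.4 and 5 cite a threshold of 150–200 min, and both levels lie above 200. With no level below or within that range and only two above it, the trial can say which of two programmes did better, not which dosage is best.

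**5. What the contrasts do identify at week 32.**

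- IG1 versus control: whether the added benefit of the 8-week programme is still present about 24 weeks after its education ends, with exercise ongoing in both arms.
- IG2 versus IG1: the effect of adding Phase 2 as a whole. Together with week 8, this shows whether benefit is maintained while reinforcement continues.
- Persistence of IG2's benefit after its programme ends: not identified, because nothing is measured after week 32.

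**The case against.** The best defence is that dose is used loosely for programme length. The Abstract and Discussion gloss it as 8 versus 32 weeks, and the Abstract and Introduction also speak of an optimal strategy, which is closer to what is tested. Section 2.4 says not primarily, so volume is secondary rather than excluded. The control arm supplies a zero level, giving three ordered levels, and attendance is recorded. Part of this stands: the arms allow a graded comparison. But the Introduction attaches minutes to the term, the step from IG1 to IG2 changes format as well as amount, and an analysis by attendance would not be a randomised comparison of doses. The absence of a dose–response model from the article is not held against it, since that may sit in an analysis plan not shown.

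A reader might infer more than the documents support:

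- *That nothing about sustained relief can be concluded, or that recency confounds IG2 versus IG1.* Continued teaching is part of the strategy that Section 2.4 and the hypothesis in Section 5 set out to test. Recency bars attribution to dose, not the comparison of strategies. IG1 versus control does bear on durability.
- *That new content such as diet and breathing explains any difference.* Session 10, given to both arms, already covers diet, and the exercise cool-down in Table 2 includes guided breathing for everyone. The argument rests on method, duration, contact and recency.
- *That a null result would be presented as an optimal dose.* Nothing says so; Section 6 is conditional on the hypotheses being confirmed.

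**Conclusion.** The point holds as a mismatch between claim and design. The claims of an isolated dose–response effect and an optimal dosage conflict with Section 2.4 and cannot be met by two non-zero programmes that differ in five respects at once. The randomisation, the endpoint and the planned contrasts are unaffected, and no estimate changes. What changes is what the trial may conclude.

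The size of the dose difference is itself unsettled: 50% or 75% more than IG1, according to which statement of Phase 2 is read. The gap in time since education at week 32 is 24 weeks in IG1 against about 0 in IG2. The IG2 figure assumes that Phase 2 runs to week 32 as Section 2.4 says; the alternative schedule gives about 8 weeks. The conclusion about dose is the same under either reading.

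**What to change.** In the Abstract, Introduction, Discussion and Conclusions, replace the dose–response, isolated-dose and optimal-dosage claims with one statement: the effect at week 32 of adding the Phase 2 reinforcement programme to 8 weeks of PNE. This follows the rationale already given in Section 2.4.

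Use sustained in two senses only:

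- for IG1 versus control, benefit of the 8-week programme about 24 weeks after its education ends;
- for IG2 versus IG1, benefit maintained to week 32 while reinforcement continues.

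Make no claim that IG2's benefit persists after its programme. The stated hypothesis does not need one, and it would require an assessment after week 32.

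Reconcile the Phase 2 frequency in Section 2.4 and Table 1 with the total of 24 sessions and 360 min in Tables 1 and 3, because both the IG2 dose and the timing of its last session depend on it.

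The cost is a narrower claim. No new arm, participant or analysis is needed.
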